### KSS

The KSS was developed to measure subjective sleepiness at any given time. It is a simple 9-point scale ranging from “extremely 1 = alert” to “9 = extremely sleepy–fighting sleep”. The scale has been validated and used frequently and provides a simple and fast measure that at the same time provides a reliable result [39]. The scale is attached in Appendix 7 in S1 Appendix.

SPS:

SPF: The estimation of fatigue will be performed using the Samn-Perelli Fatigue scale (SPF; [40]). This scale consists of 7 points and is used in aviation to assess crew fatigue. The French version comes from a report by the International Civil Aviation Organization [41]), but has not been psychometrically validated (see Appendix 6 in S1 Appendix).

Ishihara Colorblindness Test:

The Ishihara test for colorblindness [41] encompasses stimuli, that can determine the degree as well as the type of colorblindness, a person has. It will be presented in printed form, using a validated version of the test made available by the US department of infectious diseases (see Appendix 9 in S1 Appendix). Participants will be informed, that for a medically accurate test, a licensed physician is required. Should the suspicion of colorblindness arise during the assessment participants will be informed and advised to seek out a medical professional.

**The St Mary’s Hospital Sleep Questionnaire** (QSN; [42]) will be used to estimate the quality of sleep on the previous night. A translated version of this questionnaire has been produced (see Appendix 10 in S1 Appendix). The scoring of this questionnaire is not standardized due to the use of Likert scales and free responses. In addition, two questions regarding caffeine consumption have been added to this questionnaire.

Analysis Plan

The Analysis will be performed using Mixed (Multi-Level) Regression, as this allows for accounting for the effects of participants as well as tasks.

A first mixed multilevel regression will be performed on the dependent variable of RT (in MS).

The **independent Variables** are Trialtype (3 Levels), Conflict (4 Levels), Conflict Congruency (Binary) and Response (Binary)

The **dependent variable** is RT (in MS).

Time on Task (Time since task onset) will be included as a **covariate**

In a second Mixed multilevel logistic regression accuracy will be analyzed.

The **independent Variables** are Trialtype (3 Levels) and Conflict (4 Levels) and Conflict Congruency (Binary)

The **dependent variable** is Accuracy (Binary)

Time on Task (Time since task onset, and or trial number) will be included as a **covariate**

In order to account for both participants as well as task effects, both will be dummy coded and included as IV effects in the Mixed Regression for both analyses. In order to best determine the most fitting covariance structure, the analysis will first be performed with a random intercept + ARMA (or AR1). Random slopes may be added if the fixed model is reduced or following a test for slope variance of the IV effects.

Expected Results: The expected results based on the hypotheses are detailed in Table 1.

**Table 1 pone.0279021.t001:** Expected results with corresponding hypotheses.

	Hypothesis	Expected effect
Task-Switching Costs	Following a switch of the task, reaction time on said trial is higher than the average reaction time on trials of the same task where previously no switch occurred	The effect of trial-type (switch vs repeat) is significant in the Mixed Multilevel Regression (higher RT for switches)
	Following a switch of the task, accuracy on said trial is lower than the average accuracy on trials of the same task where previously no switch occurred.	The effect of trial-type (switch vs repeat) is significant in the Mixed Multilevel Logistic Regression (lower accuracy for switches)
Similarity effects	For all switch trials, reaction time will be longer if the switch occurs between dissimilar tasks	The interaction effect between trial-type (switch vs repeat) and similarity is significant in the Mixed Multilevel Regression (higher RT for dissimilar switches)
	For all switch trials, accuracy will be lower if the switch occurs between dissimilar tasks	The interaction effect between trial-type (switch vs repeat) and similarity is significant in the Mixed Multilevel Logistic Regression (lower accuracy for dissimilar switches)
Conflict effects	An incongruent stimulus will result in a higher reaction time regardless of whether the trial is a switch trial or a repetition trial.	The effect of congruency (congruent vs incongruent) is significant in the Mixed Multilevel Regression (higher RT for incongruent trials)
	An incongruent stimulus will result in a lower accuracy regardless of whether the trial is a switch trial or a repetition trial.	The effect of trial-type (congruent vs incongruent) is significant in the Mixed Multilevel Logistic Regression (lower accuracy for incongruent trials)
Mental fatigue	As time on task increases, the reaction times will increase regardless of whether the trials are switch trials or repetition trials.	The covariate of TOT is significant in the Mixed Multilevel Regression (higher RT over time)
	As time on task increases, error likelihood will increase regardless of whether the trials are switch trials or repetition trials.	The covariate of TOT is significant in the Mixed Multilevel Logistic Regression (lower accuracy over time)
	Following a switch of the task, reaction time on said trial is higher than the average reaction time on trials of the same task where previously no switch occurred	The interaction effect between trial-type (switch vs repeat) and TOT is significant in the Mixed Multilevel Regression (higher RT for switches as TOT increases)
	Following a switch of the task, accuracy on said trial is lower than the average accuracy on trials of the same task where previously no switch occurred.	The interaction effect between trial-type (switch vs repeat) and TOT is significant in the Mixed Multilevel Logistic Regression (lower accuracy for switches as TOT increases)

## 14. Inference criteria (optional)

The general inference criterion is a p-value of p < .05. In Multiple comparisons, we will adjust that criterion based on the adjusted Bonferroni criterion for multiple comparisons.

## 15. Data exclusion (optional)

To detect and reject outliers two steps will be implied. First trials with reaction times of above 5 seconds will be rejected and counted as misses. In addition, an outlier detection will be performed based on the interquartile range criterion. This will be done for trials grouped by condition.

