**Fig 2 pone.0279021.g002:**
[figure not shown]
Larger example of stimuli with cue relevant for Task 3.

During the task, participants have to perform consecutive trials, where the task and stimuli will change quasi-independently from trial to trial.

For each trial, participants are presented with 3 quasi-independent pieces of information. They are presented with an instruction for the current trial in form of the task name (eg. VERTICAL/HORIZONTAL, presented 300ms before the actual stimulus) and two stimuli in form of signs or numbers. Based on the stimuli and the instruction participants are instructed to then respond as fast as possible, using either the S or the L key on a keyboard (keys were selected as they are located at a comfortable distance on the keyboard, in order to avoid straining the hands of the participants, keys will be marked with stickers for participant ease).

In total there are 96 different conditions for each trial (4 Tasks * 3 Switching conditions * 4 Congruency Conditions * 2 Response types). However, as differences in performance of individual tasks, as well as response type, are not hypothesized to have any impact on the performance of participants, 12 main conditions remain.

*Task-Switching Conditions*:

Each trial (n) is classified into one of the three Task-Switching Conditions depending on the task in trial n-1. If the task remains the same, the trial is a repeat trial. If the task switches, but remains within the same domain (LOW/HIGH to EVEN/ODD or VERTICAL/HORIZONTAL to COLD/HOT and vice versa), it is considered an internal switch trial. Finally, switches from one domain into the other (LOW/HIGH or EVEN/ODD to either VERTICAL/HORIZONTAL or COLD/HOT and vice versa) are considered external switch trials.

Note that patterns in Task 3 are not clearly visible in the document, please refer to Fig 2.

*Congruency Conditions*:

Depending on the stimuli that are presented a trial may evoke different degrees of conflict as to the correct response required. This occurs when the **task-relevant information of the stimulus** indicates, that eg. response 1 is correct, while in the presence of a non-relevant cue biasing the response in the incorrect condition. Here 4 different conditions exist.

In the no-conflict condition, a stimulus only presents one piece of information, the relevant one. In Fig 3 the stimuli in the no-conflict condition provide no information relevant to each of the remaining 3 tasks.

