After the arrival of the participant for the first session, the participant will be asked to complete the Ishihara colorblindness test, before filling in the informed consent and information sheets. The participant will be informed, that they are permitted to ask questions at any time, and are also asked in what language they would like to perform the task (French or English). They will then fill in the Demographics questionnaire, the Edinburgh Handedness questionnaire and a KSS as well as the SPS scale. Next, the participant will be familiarized with the DTS protocol, and perform a training session, until the participants have acquired an adequate level of skill in the task.

For the training session, participants will perform at least 5 blocks (96 trials each, 3,5 min without feedback, 4 minutes with feedback) of the DTS protocol. During the first block, participants will receive feedback following each trial, to increase their individual learning rates. Subsequent blocks will exclude the feedback to completely mimic the experimental conditions. Additional blocks of training may be added following the 5 blocks to ensure adequate task performance. Additional training may be added, if the last completed block of trials, still shows a significant improvement over the preceding trial. Additional blocks will only be added with the explicit consent of the participant.

After the training session, the participant will again fill in a KSS as well as an SPS scale.

The second session will be scheduled no longer than 14 days after the first session. The procedure of the second session is largely similar to that of the first session. Participants will perform a much shorter second training session intended to help the participant remember the task. Participants will complete half a block of trials (48 trials) with feedback and another half block without feedback. Next participants will fill in a KSS and SPS scale and perform the experimental DTS protocol as detailed above. Participants will complete 5 Blocks of 336 trials each. In between blocks participants will have a short break of 28 seconds as proposed by Lim et al., 2016, to avoid recovery from the TOT effects.

Upon completion of the task participants will again fill in the KSS and SPS scale, before being thanked for their participation and paid (See Fig 5).

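### The interquartile-range outlier rule groups trials by condition but not by time on task, so it pulls the confirmatory fatigue effects on reaction time toward zero

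*Protocol article*

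**What the plan says.** Section 15 gives two steps. The first is an absolute cut: "First trials with reaction times of above 5 seconds will be rejected and counted as misses". The second is relative, and its grouping is fixed with it: "In addition, an outlier detection will be performed based on the interquartile range criterion. This will be done for trials grouped by condition". Neither the multiplier nor the scale (raw or log) is given.

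Section 7 says what a condition is: "In total there are 96 different conditions for each trial (4 Tasks * 3 Switching conditions * 4 Congruency Conditions * 2 Response types". It then collapses task and response type, which leaves 12 main conditions (3 switching × 4 congruency levels). Participant and time are in neither list. The literal reading is one pair of fences per condition, set over all people and all five blocks.

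Hypotheses 2.4.1 and 2.4.3, and the mental-fatigue rows of Table 1, make two RT effects confirmatory: RT rises with TOT, and the switch cost rises with TOT. The Analysis Plan fits RT in ms with TOT as a covariate.

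**The concern.** Deletion under this rule depends on the outcome and, through it, on the effect being tested. If RT rises over the session, late trials lie closer to a fence that is the same for the whole session, and more of them cross it. The deleted trials are the slowest ones, so the late mean is lowered more than the early mean and the estimated slope flattens. Switch trials that slow more with time lose more trials, so the interaction flattens too. Modelling participant effects, as the Analysis Plan does, cannot bring back trials already removed.

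The sizes of the fatigue effects on RT and on switch cost are at stake, and so is the reading of a small or null result: part of the shortfall could come from the trimming.

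**Working it through.** The plan gives no figure for the exclusion rule, so there is none to reproduce. The check is a simulation of the rule as written.

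**Inputs from the protocol.** Section 10: "Participants will complete 5 Blocks of 336 trials each", so 5 × 336 = 1,680 trials per person. Section 11: 30 participants, so 30 × 1,680 = 50,400 trials. With 12 balanced conditions that is 50,400 / 12 = 4,200 per condition, 4,200 / 30 = 140 per person per condition, and 140 / 5 = 28 per person per condition per block.

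**Assumed inputs (not in the protocol).** Let t run from 0 to 1 over the session, S = 1 on switch trials (two thirds of trials), and X be exponential with mean 1. The participant effect has SD 150 ms (75 and 250 ms also tried) and the noise SD is 80 ms.

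- Shift: RT = 600 + 60·S + participant + noise + 200·X + (100·t + 40·t·S)
- Slow tail: RT = 600 + 60·S + participant + noise + (200 + 100·t + 40·t·S)·X

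In both, the true average slope is 100 + 40 × 2/3 ≈ 127 ms per session and the true interaction is 40 ms. Fences are Q1 − k·IQR and Q3 + k·IQR. The slope and interaction are then estimated by within-person least squares.

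**Results at k = 1.5, SD 150 ms** (ms; change against no trimming):

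| Fence grouping | Slope, shift | Slope, tail | Interaction, shift / tail |
|---|---|---|---|
| No trimming | 127.7 | 126.9 | 40.2 / 39.4 |
| Condition (as written) | 118.7 (−7%) | 79.1 (−38%) | 37.0 / 22.6 |
| Condition × participant | 114.4 (−10%) | 68.0 (−46%) | 36.0 / 20.1 |
| Condition × block | 126.9 (−1%) | 102.8 (−19%) | 39.4 / 30.5 |
| Condition × participant × block | 126.8 (−1%) | 104.6 (−18%) | 39.8 / 31.6 |

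**Where the trials go (condition only).** Block 1 loses 1.9% (shift) or 1.5% (tail); block 5 loses 3.0% or 5.4%. The slowest five people lose 5.7% or 6.5%; the fastest five lose 0.9% or 1.5%.

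**Range.** Other assumed settings at 1.5 × IQR widen the slope loss to about 6–10% (shift) and 27–45% (tail). The low end of the tail range comes from a setting with mean RT about 800 ms, between-person SD 180 ms and a true slope near 60 ms, where the slope fell from 59 to 43 ms: (59 − 43)/59 = 27%. At 3 × IQR the loss is about 1–2% (shift) and 11–17% (tail). If slower people are also assumed to fatigue more, the tail loss at 1.5 × IQR reaches (127.7 − 67.0)/127.7 = 48%.

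**No true TOT effect.** The slope is −0.2 ms untrimmed and −0.1 ms trimmed, and blocks 1 and 5 each lose 2.4%. No spurious trend appears.

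**Log fences within participant × condition × block.** In a separate run on assumed parameters at 1.5 × IQR, the slope was 78 of 80 ms (shift, −2.5%) and 72 of 79 ms (tail, −9%), against losses of about 6% and 37% there under the rule as written.

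**The case against.** The strongest reply is that no conclusion need change. Table 1 judges the fatigue hypotheses by significance and direction, not by slope size. In a simulation with independent residuals and no variation in slopes between people, the trimmed slope was 56 ms (SE 2.9) under a shift and 42 ms (SE 3.2) under a tail effect, each more than 12 standard errors from zero. That stands as far as it goes. Autocorrelated errors or random slopes, both of which the Analysis Plan contemplates, would widen the standard errors. The interaction is the smaller effect and loses a similar share.

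It can also be said that the text does not state outright that fences are pooled over people and time. That is true; it is the literal reading of a grouping that names condition alone.

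A reader might infer more than the protocol supports:

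- *That pooling over people causes the attenuation.* It does not. Fencing within participant but not block shrinks the slope slightly more. The cause is that time is left out; pooling over people explains only the uneven loss between slow and fast participants.
- *That slow or late data are deleted wholesale.* Block 5 loses about 3–5% of its trials in the main runs.
- *That error trials stay in the RT model.* Section 15 neither keeps nor removes them, and a condensed article may leave this to a fuller plan.
- *That switch and repeat are misclassified after errors.* Section 7 says "Each trial (n) is classified into one of the three Task-Switching Conditions depending on the task in trial n-1", and each trial displays its task, so the natural reading is the instructed task, whatever the participant did.
- *That the first trial of each block matters.* It is 5 of 1,680 trials, or 0.3%.

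**Conclusion.** The point holds in a limited form. As written, the IQR step ignores time on task in a study whose confirmatory hypotheses include slowing over time. If that slowing is real, the TOT slope and the trial-type by TOT interaction on RT are biased toward zero, and slow participants lose more trials than fast ones. The direction does not depend on the particular parameters tried; the size does. It ranges from about 1% (3 × IQR, whole-distribution shift) to about 45% (1.5 × IQR, slow-tail fatigue). All these figures rest on assumed RT distributions, because the protocol gives none, and on a multiplier that it does not state.

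The error is conservative: the rule cannot manufacture a fatigue effect. The consequence is an understated effect and a less interpretable null. This should be corrected, but it does not threaten the validity of a positive fatigue result.

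**What to change.** In section 15:

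1. State the IQR multiplier.
2. Compute the fences on log RT, because raw RT is typically right-skewed, within participant × condition × block, with condition meaning trial type × conflict. Block removes most of the bias and participant evens out the loss between slow and fast people. Conflict must stay in the grouping: dropping it shrank an assumed 80 ms conflict effect to about 72–74 ms.
3. Apply this trimming to the RT model only.
4. Report the RT model without IQR trimming, keeping the 5-second cut, as a sensitivity analysis. Block-wise fences remove only part of the bias if fatigue lengthens the tail, so this check is needed even with the new grouping.

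The cost is a few lines of wording and code and one extra model. Cells are small, about 28 trials each, so individual fences are noisier. On raw RT the finer grouping also removed more trials overall (4.8–5.1%, against 2.4–3.3% for condition only), though evenly across blocks and people. Section 9 says registration precedes data creation, so the change can be made without knowledge of results.

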## 11. Sample size (required)

The approximate range of required participants was determined using G*Power [37] Based on the reported statistics [3,15]. Their reported effect sizes ranged from 0.84 to 1.81 (f-squared). For a one-tailed test with an alpha of 0.05. The sample size required ranges from 15–25 participants. These numbers are only approximations, as the effects that we intend to observe are not exactly the same as the ones reported in the aforementioned studies. We intend to collect data from 30 participants, in order to assure an adequate effect size.

Variables

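### Setting the IQR outlier fences separately within the conditions being compared pushes the RT switch, similarity and conflict-level tests above the stated 5%: about 9–14% with 1.5 × IQR, right-skewed RT and fences pooled over participants

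*Protocol article*

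**What the plan says.** Section 15 of the protocol article removes trials in two steps. The first is a fixed 5 s limit, the same for every condition. The second is data-driven: "In addition, an outlier detection will be performed based on the interquartile range criterion. This will be done for trials grouped by condition". Neither the IQR multiplier nor whether the grouping runs across or within participants is stated.

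Section 7 builds its 12 main conditions from three switching levels and four conflict levels. A fuller count of 96 adds task and response type. Neither count includes whether the irrelevant cues are congruent or incongruent. In the Analysis Plan, the RT model's independent variables "are Trialtype (3 Levels), Conflict (4 Levels), Conflict Congruency (Binary) and Response (Binary", so trial type and conflict level both define the outlier groups and are tested. That model starts from a random intercept with an ARMA or AR1 error structure; random slopes are optional. Section 14 sets the error rate: "The general inference criterion is a p-value of p < .05".

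**The concern.** An exclusion limit that does not depend on the factor under test is harmless under the null. The kept trials are a sample from one truncated distribution, and the usual standard error describes them. When each condition estimates its own quartiles and fence, this no longer holds. A condition that is slow by chance gets a higher fence and keeps more slow trials; a fast one loses more. The chance difference survives trimming while the residual SD, and with it the reported standard error, falls.

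More trials do not help, because the error in the fence and the error in the mean shrink at the same rate. At stake are the RT tests of hypotheses 2.1 (switch cost) and 2.2 (similarity, the stated aim of the study), and any RT contrast between conflict levels. Their p-values would be too small and their confidence intervals too narrow.

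**Working it through.** **Inputs from the article.** Section 11: "We intend to collect data from 30 participants". Section 10: "Participants will complete 5 Blocks of 336 trials each". Hence 5 × 336 = 1,680 trials per participant and 30 × 1,680 = 50,400 in all. With 3 × 4 = 12 balanced conditions that is 1,680 / 12 = 140 trials per participant and condition, or 50,400 / 12 = 4,200 per condition. Nominal level: 0.05.

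**Assumptions, because the article is silent.** Multiplier 1.5 (3 also tried); RT distribution; fences pooled over participants or set within them; two-sided tests (section 14 gives no sidedness, while section 11 sizes the study "For a one-tailed test with an alpha of 0.05"). There is no true effect unless stated. The AR/ARMA errors and the 5 s limit were not modelled.

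Two simulations were used. A: lognormal (sigma 0.3 and 0.4) and ex-Gaussian RT, 1,000–2,500 replicates. B: ex-Gaussian (SD 60, tau 200), lognormal (log-SD 0.35 and 0.5) and normal RT, 1,500 replicates. The Monte Carlo error in B is √(0.05 × 0.95 / 1,500) = 0.6 points at 5% and √(0.14 × 0.86 / 1,500) = 0.9 points at 14%. Unless stated, the test is at trial level with participant intercepts.

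**Step 1: reproduce the stated 5%.** With no IQR exclusion, A gives 4.7–5.0% and B 4.2–5.9%.

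**Step 2: fences by the 12 conditions, pooled over participants, 1.5 × IQR.** False positives in B (%):

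| RT distribution | Switch | Similarity | Conflict level (highest v none) |
|---|---|---|---|
| Ex-Gaussian | 12.9 | 12.8 | 12.5 |
| Lognormal 0.5 | 13.7 | 11.6 | 13.9 |
| Lognormal 0.35 | 10.3 | 8.6 | 11.1 |
| Normal | 6.1 | 5.5 | 6.7 |

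A gives 9.8%, 11.6% and 12.4% for similarity (sigma 0.3, sigma 0.4, ex-Gaussian). With 3 × IQR, A gives about 5–7% and B about 7.1%. For skewed RT at 1.5 × IQR, the multi-degree-of-freedom tests in B gave 11–17% (trial type) and 13–18% (conflict level).

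**Step 3: confirm the mechanism.** If the reported SE understates the true SD of the contrast, the two-sided rate is 2 × [1 − Φ(1.96 × SE / SD)]. From A, in ms:

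- 3.50 / 4.15 = 0.843, giving 2 × [1 − Φ(1.653)] = 9.8%
- 4.63 / 5.78 = 0.801, giving 2 × [1 − Φ(1.570)] = 11.6%
- 3.05 / 3.89 = 0.784, giving 2 × [1 − Φ(1.537)] = 12.4%

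These match the simulated rates, so an SE 16–22% too small accounts for the inflation. For one-tailed 5% tests the same ratios, with 1.645 in place of 1.96, give 8.3%, 9.4% and 9.9%.

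**Step 4: vary grouping and model.** With participant × condition fences at 1.5 × IQR, the random-intercept test in B gives about 16% (ex-Gaussian), 9.5–14.6% (lognormal) and 6–8% (normal). The same fences tested on participant means give 4–6%. With pooled fences, participant-level tests in A give 10.6–12.2% when the effect does not vary between people and 7–9% when it varies with an SD of 25 ms.

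**Step 5: congruent versus incongruent.** With pooled fences by the 12 conditions, B gives 4.5–4.9%. With congruency added to the grouping (24 cells) and skewed RT, it gives 9–14%.

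**Step 6: condition-blind fences.** One fence per participant gives 4.4–5.0% in A. In B, blind fences, overall or per participant, give 4.3–6.3%.

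**The case against.** By-condition fences have a rationale: they avoid over-trimming the slower condition. For a 3% proportional slowing (lognormal, sigma 0.4), one run gave 32.6 ms untrimmed, 31.2 ms with by-condition fences (31.2 / 32.6 = 0.957, a 4% loss) and 25.3 ms with a blind fence (25.3 / 32.6 = 0.776, a 22% loss). This stands. The choice trades calibration under the null against attenuation of the effect, and the cost belongs beside the fix.

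Section 15 can also be read as participant × condition fences, and the Analysis Plan allows random slopes. Under that combination inflation is essentially absent: 5.2–5.6% on participant differences, or 5.6–8.3% against 5.2–7.2% untrimmed when the effect varies between people with an SD of 25 ms. This stands too, but the plan commits to neither part, and its starting model with those fences gave the highest single-contrast rates.

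A reader might also infer more than the documents support:

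- *That every RT test, including hypothesis 2.3, is inflated.* Table 1 tests 2.3 by congruency, which is not one of the 12 conditions.
- *That similarity is the most exposed contrast.* A null error rate does not depend on expected effect size, and similarity was at or slightly below switch in most settings.
- *That chance differences are strongly amplified.* The contrast SD rose only from 4.93 to 5.17 ms (lognormal) and from 2.30 to 2.37 ms (ex-Gaussian), or 3–5%. The main fault is the understated SE.

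**Conclusion.** The point holds for the RT switch and similarity tests and for RT contrasts between conflict levels. Section 15 actively ties the exclusion limits to the factors under test, and nothing in the article corrects for it.

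The size is conditional. It is about 9–14% with 1.5 × IQR, right-skewed RT and pooled fences, and about 5–7% with 3 × IQR or near-normal RT. It reaches about 16% with participant × condition fences under the random-intercept model, and is about 4–6% with those fences when the test uses between-participant variation in the effect. No single figure can be attached to the plan, because the multiplier, RT distribution and pooling rule are not given. Table 1's congruency test is affected only if congruency joins the grouping. The accuracy model was not examined.

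A separate matter should not be mixed in. If the effect truly varies between people (SD of 20–40 ms assumed), an intercept-only model inflates the switch and similarity tests to 25–67% with no exclusion at all. Changing the fence does not address that.

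**What to change.** In section 15, replace the second sentence of the quoted rule with: *The fence is computed once per participant from all of that participant's trials, without regard to trial type, conflict or congruency.* State the multiplier. Name this as the primary analysis and the untrimmed effect, after the 5 s limit, as a sensitivity analysis, so that no choice between the two remains open.

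The change is one sentence and one line of code; section 9 places registration before data creation. Its real cost is attenuation in ms: 18.1 against 20.0 untrimmed for an additive effect (18.1 / 20.0 = 0.905, about 10% smaller) and 28.6 against 36.4 for a 3% proportional effect (28.6 / 36.4 = 0.786, about 20% smaller). Power for a 20 ms effect was 79% with the blind fence against 76% untrimmed (lognormal, sigma 0.4), and 94% against 91% (ex-Gaussian), so essentially none is lost.
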